#### Care as usual

Care as usual (CAU) consists of a 1.5 h-session of psycho-education on healthy lifestyle for the parents only. This psycho-education consult is given by a psychologist which is trained for this research. The children have to follow an e-health psycho-education module about healthy lifestyle on a device of their choice (e.g., a mobile phone, laptop, or tablet), which will take them about two hours (in total) to complete. However, this module does not have to be taken through in one go. As well as for the psycho-education consult of parents as for the e-health module of the children, the content consist of information on healthy eating behavior, healthy use of screen time, healthy sleep patterns, and physical exercise. A conscious decision was made to include psycho-education about a healthy lifestyle in the control condition. We decided to offer parents and children in the CAU group a psycho-education session on healthy living and access to the e-health psycho-education module in exchange for the information we gather during assessments. After this, the child and family will receive care as usual (e.g., optimization of pharmacotherapy).

### Outcomes

Outcome parameters and measurement times are assessed as shown in Table 2.

**Table 2 Tab2:** Outcome parameters from baseline to 12 months after baseline

Measurement	T0^a^	T1^b^	T2^c^	T3^d^	Instrument
*Descriptives*					
A. Descriptives	T0				Intake questionnaire
B. Psychiatric evaluation	T0				DSM-V
C. Intelligence quotient (IQ)	T0				WISC-V
*Primary outcome*					
D. Quality of life	T0	T1	T2	T3	Kidscreen-27
*Secondary outcomes*					
E. Emotional and behavior problems	T0	T1	T2	T3	CBCL
F. Cognitive performance	T0	T1			COTAPP
G. Somatic measurements	T0	T1		T3	Somatic screening
H. Blood laboratory tests	T0				Blood samples (15 ml) sober
*Lifestyle parameters*					
I. Sleep: Sleeping habits	T0	T1	T2	T3	CSHQ
J. Sleep: Sleeping dairy	T0	T1	T2	T3	Sleep–wake diary
K. Sleep: 24 h sleep/wake measurements	T0	T1	T2	T3	Actigraphy
L. Diet: Food consumption	T0	T1	T2	T3	Nutrition diary
M. Diet: Eating habits	T0	T1	T2	T3	Eating habits questionnaire
N. Physical activity: Physical fitness	T0	T1		T3	Shuttle run test
O. Physical activity: Physical activity	T0	T1	T2	T3	Physical activity questionnaire
K. Physical activity: Actigraphy	T0	T1	T2	T3	Actigraphy
P. Screen time: Screen activities	T0	T1	T2	T3	Screen time questionnaire
*Measurements of costs*					
Q. Used healthcare resources				T3	Tic-P questionnaire
*Other study parameters*					
R. Parenting styles	T0	T1	T2	T3	VSOG
S. Parenting functioning	T0	T1	T2	T3	VGFO
T. Prior beliefs	T0				5-item questionnaire
U. Patient satisfaction			T2	T3	GGZ-Jeugdthermometer

*DSM* Diagnostic and Statistical Manual of Mental Disorders, *WISC* Wechsler Intelligence Scale for Children, *IQ* Intelligence quotient, *CBCL* Child Behavior Checklist (6–18), *CSHQ* Children’s sleep habit questionnaire, *Tic-P* Trimbos and iMTA questionnaire on Cost associated with Psychiatric illness, *VSOG* Verkorte Schaal voor Ouderlijk Gedrag, *VGFO* Vragenlijst Gezinsfunctioneren Ouders

^a^T0 Baseline

^b^T1 twelve weeks after baseline

^c^T2 six months after baseline

^d^T3 twelve months after baseline

#### Descriptives

A. DescriptivesThe children’s primary caregivers are asked to report personal characteristics for themselves (gender, age, country of birth, highest completed education, family composition, living situation, and occupational status), their partner - if any (gender, age, country of birth, most increased completed education and occupational status)- and the child (country of birth, medical history, and school parameters).B. Psychiatric evaluationBased on the Diagnostic and Statistical Manual of Mental Disorders, Fifth Edition (DSM-5) [24] the psychiatric diagnosis is assessed by a multidisciplinary team consisting of child and adolescent psychiatrists, psychologists, and nurse practitioners. For the descriptives, a primary diagnosis is presented. Other diagnoses are grouped as co-morbidity. This is standard practice at Karakter Child and Adolescent psychiatry.C. Intelligence quotientTotal IQ is estimated using the Wechsler Intelligence Scale for Children (WISC-5), the best-known and most widely used intelligence test in the Netherlands for children [25]. The WISC-V is suitable for children from 6 to 16 years. WISC-V will only be administered if it hasn't been taken in the past two years. Otherwise, the outcomes from a previous WISC-V are used. IQ is assessed only at T0 (Baseline).

#### Primary outcome

D. Quality of lifeParents are invited to rate the children’s quality of life using the KIDSCREEN-27 [26]. The KIDSCREEN-27 is a generic health-related quality of life (HRQOL) questionnaire for children and adolescents applicable for healthy and chronically ill children and adolescents aged between 8 and 18 years [26]. The KIDSCREEN-27 consists of 27 items that measure five dimensions: physical well-being, psychological well-being, parent relations & autonomy, social support & peers, and school environment. Items are answered on a five-point Likert-type scale assessing frequency: *never* (1), *seldom* (2), *sometimes* (3), *often* (4), and *always* (5), or intensity: *not at all* (1), *slightly* (2), *moderately* (3), *very* (4), and *extremely* (5), with a 1-week recall period. Scores are coded from 1 to 5, negatively formulated items will be recoded, and the sum scores for respective dimensions are transformed to* T* scores with a mean of 50 and a standard deviation (SD) of 10: higher scores indicate better HRQOL [26]. The KIDSCREEN-27 has been shown to have robust psychometric properties [26]. The internal consistency of the domains was between 0.81 and 0.84, and the test-retest reliability of the domains ranged from 0.61 to 0.74 [26]. Quality of life is assessed at T0 (Baseline), T1 (end of intervention), T2 (six months after baseline), and T3 (12 months after baseline).

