The primary objective of the Movementss study is to quantify the short-term (after 12 weeks) and long-term (after 6 and 12 months) effectiveness on quality of life compared to care as usual (CAU) in children aged 6–12 years with MI. We hypothesize that the lifestyle intervention will be more effective than CAU. The second aim is to examine the short- and long-term effects of the lifestyle intervention compared to CAU on outcome measures related to mental and physical symptoms and lifestyle problems such as emotional and behavioral problems, cognitive outcomes, sleeping, eating patterns, and weight status. It is hypothesized that lifestyle improvement will have a positive effect on these mental and physical symptoms. Additionally, the third aim is to investigate the cost-effectiveness of the lifestyle intervention compared with CAU. We assume that intervening in lifestyle at such a young age will result in less expensive care in the long term. Also, this study aims to identify potential moderators of adherence or responders to the treatment (e.g., SES, ethnicity, comorbidity). Finally, qualitative questions will be addressed in this study by examining the potential facilitators and barriers to the lifestyle intervention.

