### Sample size and power

A sample size calculation using G-power 3.1 was conducted for the primary outcome measure, defined as the mean difference in the quality of life between two groups at three time points (baseline, 12 weeks intervention, 26 weeks follow-up). We used historical data on the Kidscreen-27 (a measure of QoL) from our own population to estimate the effect size. To detect a median effect size (Cohen’s f = 0.39) with a two-sided significance level of 5% and power of 80% with equal allocation to two arms would require 66 patients in the trial. To allow for 20% drop-out, 80 children are recruited in total.

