### Statistical analysis

Data will be analyzed using SPSS V.29.0 for Windows (SPSS Incorporated). Descriptive statistics will be performed for baseline characteristics of the study population. Parametric data will be presented as means with SD, and non-parametric distributed variables as median with interquartile ranges (IQRs). A *p*-value < 0.05 will be considered statistically significant. To evaluate the impact of missing data on the outcome measurements, different approaches will be used, such as Multiple Imputation Strategy.

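### The primary endpoint is not fixed to one score and one contrast, so the 5% error rate behind the sample size is not secured

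*Protocol article*

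**What the plan says.** **Score.** Under Primary outcome: "The KIDSCREEN-27 consists of 27 items that measure five dimensions". The scoring rule works at that level: "the sum scores for respective dimensions are transformed to" T scores with mean 50 and SD 10. No total, index or primary dimension is given. For the CBCL, by contrast, the article does say which subscales combine into internalizing, externalizing and total scales.

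**Visits.** The Background sets the primary objective as "to quantify the short-term (after 12 weeks) and long-term (after 6 and 12 months) effectiveness on quality of life". The Primary outcome section agrees: "Quality of life is assessed at T0 (Baseline), T1 (end of intervention), T2 (six months after baseline), and T3 (12 months after baseline"). Sample size and power instead defines the primary outcome as the mean difference in quality of life "at three time points (baseline, 12 weeks intervention, 26 weeks follow-up"), which leaves out 12 months. The background part of the Abstract names 12 weeks and 1 year, which leaves out 6 months.

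**Decision rule.** Statistical analysis gives one general threshold: a p-"value < 0.05 will be considered statistically significant". Primary study parameter(s) promises repeated-measures techniques for the arm difference in quality of life, without naming a score, a contrast or the visits. The sample size assumes a two-sided 5% level.

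**The concern.** The sample size buys 80% power at 5% for one test. That 5% describes the trial only if one test, chosen beforehand, answers the primary question. Here the score is open (five candidates and no aggregate), and the article gives conflicting sets of visits.

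A claim of success could therefore rest on whichever dimension or visit looks best, with no rule in the text against it. The risk is sharper in this trial because families, researchers and practitioners all know the allocation and the parents do the rating. If the 12-month visit belongs to the primary question, as the Background says, the power statement does not cover it.

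**Working it through.** **1. Reproducing the stated 66.** Inputs from Sample size and power: Cohen's f = 0.39, two-sided 5%, 80% power, two equal arms, three time points. The article does not say which G*Power test was used. The closest match is the multivariate group-by-time test, with k = 2 arms and m = 3 time points:

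- numerator df = m − 1 = 2
- denominator df = N − k − m + 2 = 66 − 3 = 63
- noncentrality λ = f² × N = 0.1521 × 66 = 10.04
- critical F(2, 63) at 5% = 3.14
- power = P(noncentral F > 3.14) = **79.7%**; the smallest even N that reaches 80% is 68

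Other variants with f = 0.39 are further away:

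| Variant | Total N |
|---|---|
| One-way comparison of two groups | 54 |
| Between-arm repeated-measures factor, 3 time points, correlation 0 to 0.99 | 20 to 54 |
| Univariate interaction, 3 time points | 24 or fewer |
| Interaction with the SPSS effect-size option | 36 |

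So 66 fits one score, one test and no 12-month visit.

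**2. Adding the 12-month visit.** Same test with m = 4:

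- df = 3 and 66 − 2 − 4 + 2 = 62; λ is still 10.04; critical F = 2.75
- power = **73%** at N = 66; N = 76 is needed for 80%

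**3. Family-wise error if several scores or visits are tested at 0.05.** For K independent tests the error is 1 − 0.95^K:

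- K = 5: 1 − 0.774 = 22.6%
- K = 10 (5 dimensions × 2 follow-ups): 1 − 0.599 = 40.1%
- K = 15 (5 × 3): 1 − 0.463 = 53.7%

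The dimensions and visits will be correlated, and the article gives no correlations. The lower figures come from simulated multivariate normal test statistics with assumed correlations.

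| Testing scheme | Correlated, dimensions 0.3–0.7, visits 0.5–0.7 (assumed) | Independent |
|---|---|---|
| One score, one omnibus test | 5% | 5% |
| One score, 2 visits separately | 8–9% | 9.8% |
| One score, 3 visits separately | 11–13% | 14.3% |
| Five dimensions, one test each | 15–21% | 22.6% |
| Five dimensions × 2 visits | about 23–35% | 40.1% |
| Five dimensions × 3 visits | 30–46% | 53.7% |

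**4. Price of adjusting instead of choosing.** If all five dimensions stayed primary with Bonferroni, each would be tested at 0.05/5 = 0.01. With the 2-df test and f = 0.39, power at N = 66 falls to 57%, and N = 96 is needed for 80%.

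**The case against.** A reader might infer that the article plans 10 to 15 primary tests, each read at p < 0.05, and hence that the 5% level fails by as much as a factor of ten. The text does not support this. The sample size and primary analysis sections both refer to quality of life in the singular. The 0.05 threshold is a general convention, not a rule that any one of many results makes the trial positive. The scoring paragraph describes an instrument and does not list tests. Repeated-measures techniques also allow one omnibus test over all visits, which does not multiply by visit.

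Two further objections carry weight. The figures of 40% and 54% need independence, which is implausible for the same children, rater and questionnaire. And a condensed article may leave multiplicity rules and model details to a full protocol or analysis plan, so their absence here is not an error.

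What remains is in the printed text. An unseen document cannot make the Background and the sample size section agree on the primary visits. The score called primary is described only as five separate scores. Even on the kindest view of visits (one omnibus test per dimension), five dimensions leave about 15–23% unless one score is named.

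**Conclusion.** Wrong as written. The primary endpoint is not one identified quantity, and the sections contradict each other on its visits. The 5% behind the 66 children is therefore not secured, which is a weaker statement than that it is breached.

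- **Not conditional on how testing is done:** the conflict over visits, and five dimension scores with none marked primary.
- **Conditional on an inferred G*Power option:** the match to one 2-df test (79.7%) and the drop to about 73% with the 12-month visit.
- **Conditional on separate testing:** about 15–23% for five dimensions (between-dimension correlation 0.7 down to 0), about 23–40% with two visits, and 30–54% with three. The lower ends use assumed correlations of 0.7; the upper ends assume independence. With one named score and one omnibus test the rate stays at 5%.

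One separate matter does not bear on the error rate. The instrument is described as applicable to children and "adolescents aged between 8 and 18 years", while the Participants section enrols ages 6–12. The article does not say that the youngest children cannot be scored, but it does not address the gap either.

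**What to change.** Before any analysis by arm:

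1. Name one primary score: either one KIDSCREEN-27 dimension, or a composite defined in advance such as the mean of the five T scores. The composite is only an option; the article describes no such score and gives no validity data for it.
2. Name one primary contrast: either the arm difference at one stated visit, or one omnibus repeated-measures test over a stated list of visits. The choice belongs to the sponsor, since the Background gives 12 weeks, 6 months and 12 months equal standing.
3. Make the Abstract, Background, Primary outcome, Sample size and power, and Primary study parameter(s) agree with that choice.
4. Restate the power for that contrast.
5. Treat the remaining dimensions and visits as secondary, tested in fixed order or with Holm adjustment.
6. Separately, repeat the primary contrast in children aged 8–12 as a sensitivity analysis.

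The cost is wording and a recalculation, with no new data. The downside is that claims on single dimensions or later visits face a stricter or ordered test; with Holm over five dimensions the first step is at 0.05/5 = 1%. If the 12-month visit joins an omnibus test of the kind matched above, the sponsor must accept about 73% power at 66 children or justify a different effect size.

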#### Secondary outcomes

E. Emotional and behavioral problemsThe Dutch parent-report version of the Child Behavior Checklist 6–18 years (CBCL) assesses a wide range of children's emotional and behavioral problems, aiming to identify children at high risk of a psychiatric disorder [5]. The CBCL/6–18 comprises 120 items assessing behavioral and emotional problems that are answered on a 3-point Likert-type scale (0 = *not true,* 1 = *somewhat or sometimes true,* 2 = *very true or often true*) by parents [5]. The scores display eight problem scales: withdrawn (1); somatic (2); anxious (3); social (4); thought (5); attention (6); rule-breaking (7); aggressive (8); and other problems, the sum of the problem scale 1,2 and 3 form the scale ‘internalizing behavior’; 7 and 8 form ‘externalizing behavior’ [5]. All subscales together count for the total problem scale [5]. Some items contribute to more than one problem scale. T scores are computed from raw scores; higher scores on the syndrome scales indicate greater severity of problems. A T score of 63 (90th percentile) demarcates the clinical range, indicating that a child needs professional help [5]. The CBCL/6–18 has well-established psychometric properties in clinical, non-clinical, and cross-cultural populations [27]. The CBCL is assessed at T0 (Baseline), T1 (end of intervention), T2 (six months after baseline), and T3 (12 months after baseline).F. Cognitive performanceThe Cognitive Task Application (COTAPP) measures cognitive performance [28]. As described by Bosch, Bierens [29], this Dutch neurocognitive assessment tool is designed to examine (variability in) processing speed, attentional and executive control, working memory, and learning speed with a computer task. The COTAPP is a two-choice reaction time paradigm with seven blocks, in which the child is assisted through the different paradigms in a playlike way [28, 29]. By default, no coaching or help is given to the child. If the child fails in completing the task without the assistance of the examiner, coaching or help can be provided in a structured manner [28, 29]. The amount of offered coaching or help, is coded by the examiner and included in the outcome parameters [28, 29]. In addition, the level of verbal and motor activity of the child during performance can be coded. Validity and reliability of the COTAPP have been confirmed [28], with COTAPP relating significantly to intelligence, school performance, ADHD and Autism Spectrum Disorder symptoms, and the quality of the student-teacher relationship [29]. The COTAP is assessed at T0 (Baseline) and T1 (end of intervention).G. Somatic measurementsPhysical examination includes measurement of weight, height, blood pressure, heart rate, head circumstances, an inspection of dysmorphic features, and moto coordination are routinely assessed at start of treatment (T0) by a nurse specialist supervised by a child and adolescent psychiatrist as part of standard clinical care. A subset of the somatic screening (height, weight, waist circumference, blood pressure) is assessed at T1 and T3.Overweight and obesity prevalence for children are defined by the cut-off values on body mass index references and age according to the International Obesity Task Force [30]. In the United States and Europe, the diagnosis of persistent childhood hypertension is made when repeat blood pressure values on three separate visits are greater than the 95^th^ percentile for the age, gender, and height of the patient or ≥130/80 mmHg. The somatic measurements are assessed at T0 (Baseline), T1 (end of intervention), and T3 (12 months after baseline).H. Blood laboratory testsBlood samples (15 ml) are assessing glucose, HbA1C, total cholesterol, lipid profile, prolactin, vitamin D, thyroid stimulation hormone, and ALAT at T0 (Baseline) and for children with abnormalities during treatment , which are processed at local laboratory facilities. References from these facilities are used to interpret the results of the laboratory findings. For vitamin D, references from the American Academy of Pediatrics Committee on Nutrition and The Institute of Medicine are used corresponding to a serum 25-hydroxyvitamin D level of at least 50 nmol/liter (e.g., insufficiency <50-75 nmol/ml; deficiency <50nmol/l) [31–33].

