#### Randomization

The Movementss study is a two-arm randomized controlled trial; patients fulfilling eligibility criteria and willing to participate will be randomized after baseline assessment (1:1 allocation ratio) in either the lifestyle intervention or CAU group using block randomization, with varying random block sizes of 2, 4 or 6. A priori, an independent statistician will prepare a computer-generated randomization schedule stratified for weight (underweight, normal, overweight), sex (male, female), and age (6–8 years, 9–12 years) to ensure that the number of participants in both treatment arms is closely balanced within each stratum. Castor EDC will be used for the actual randomization process. After obtaining informed consent and baseline measurements, the study coordinator will provide the randomization code. Participants, researchers, and practitioners are aware of treatment allocations.

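### The COTAPP outcome parameters include help that the examiner both gives and codes, and the plan provides no masked examiner at T1, the only COTAPP test after randomisation

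*Protocol article*

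**What the plan says.** Under Secondary outcomes, item F, the protocol article describes COTAPP as a two-choice reaction-time test covering processing speed, attentional and executive control, "working memory, and learning speed with a computer task". Help is an exception: "By default, no coaching or help is given to the child". The exception is then set out: "If the child fails in completing the task without the assistance of the examiner, coaching or help can be provided in a structured manner". The next sentence makes that help part of the result: "The amount of offered coaching or help, is coded by the examiner and included in the outcome parameters". Finally, "the level of verbal and motor activity of the child during performance can be coded"; no coder is named for this, and it is not expressly called an outcome parameter.

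Table 2 and item F place COTAPP at T0 and T1 only. The Procedures section places both visits on site at the clinic. The Randomization section puts allocation after the baseline assessment and states: "Participants, researchers, and practitioners are aware of treatment allocations". It makes no exception for outcome testing.

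**The concern.** One person judges that a child cannot finish unaided, gives the help, codes how much was given, and thereby produces an outcome value. If that person knows the arm at T1, expectation can enter in two ways:

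- **Coding.** The same amount of help can be recorded as more or less.
- **Delivery.** Help can be offered more readily in one arm, which may change the task performance that the computer then records.

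Cognitive outcomes belong to the trial's second aim, and no later COTAPP test exists against which a biased T1 value could be checked. Parents who rate quality of life cannot be masked in this trial. A tester at a clinic visit can be, at least in principle, so this source of bias is partly avoidable.

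**Working it through.** The protocol gives no figure for assessor bias, so there is nothing to reproduce. The point rests on reading the sections together.

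1. **Does an examiner-produced value count as an outcome?** Yes for help, by express statement in item F. For verbal and motor activity, only if it is coded and used.
2. **Does the examiner know the arm?** Item F does not identify the examiner. The statement in the Randomization section covers all researchers and practitioners, and no masked assessor appears elsewhere. On the text as it stands, the examiner is not masked.
3. **Which measurement is exposed?** T0 is completed before randomisation, so the arm cannot influence it. T1 is the only COTAPP test after randomisation, so the exposure falls on the T1 value and hence on any change from T0.
4. **Which parameters are exposed?** The help code directly, and the activity code if used. Speed, variability and accuracy are exposed only indirectly, through unequal help.

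To show what a bias would do, suppose there is no true effect and a difference of *b* SD between arms at T1 that arises only from the examiner. This is an assumption; the documents give no value for *b*.

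- Inputs: two-sided 5% level; *n* = 66/2 = 33 per arm (the required number in Sample size and power) or *n* = 80/2 = 40 per arm (the number recruited).
- Shift in standard-error units: δ = *b* / √(2/*n*) = *b* × √(*n*/2). For *n* = 33, √16.5 = 4.062; for *n* = 40, √20 = 4.472.
- False-positive rate: Φ(δ − 1.96) + Φ(−δ − 1.96).

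| *b* (SD) | δ, *n* = 33 | rate | δ, *n* = 40 | rate |
|---|---|---|---|---|
| 0.1 | 0.406 | 6.9% | 0.447 | 7.3% |
| 0.2 | 0.812 | 12.8% | 0.894 | 14.5% |
| 0.3 | 1.219 | 23.0% | 1.342 | 26.9% |

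The rates apply to one examiner-dependent parameter tested alone. A normal shift is a rough model for a code whose default is no help, and the share of children who need help is not given.

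**The case against.** The strongest reply is that this is a small corner of one secondary outcome. The test runs on a computer, unaided completion is the rule, and help follows a structure. Coding the help is itself a safeguard: extra help that is honestly coded becomes visible in the help code. To lift performance unseen, an examiner would have to help more and also under-record it. The article is a condensed account, and the full protocol may say who tests the children. The order of importance of the COTAPP parameters may also be set in an analysis plan that is not shown.

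Much of this stands, and it narrows the point. It does not remove it, because the examiner still judges that the child has failed, still chooses the code, and is covered by a statement of awareness that allows no exception. That statement is a stated design choice and not a detail left out.

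A reader might infer more than the text supports:

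- **That COTAPP is as open to bias as a parent questionnaire.** It is not; most of it is recorded by the computer.
- **That the examiner may have treated the child.** Nothing says so.
- **That activity ratings are an established examiner-scored outcome.** The text makes them optional and names no coder.
- **That COTAPP was meant as the objective check on the parent-reported outcomes.** It is the only performance-based mental outcome repeated after randomisation, since KIDSCREEN-27 and CBCL are parent-rated and the WISC-V is given at T0 only. The protocol, however, gives it no corroborating role.

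**Conclusion.** The point holds in a limited form. As written, the plan lets an examiner who is not masked produce an outcome parameter at the only COTAPP test after randomisation. Direct bias is confined to the help code and, if used, the activity code; an indirect effect on task performance through unequal help is possible. The size cannot be determined from the documents. The range of about 7% to 27% depends wholly on the assumed shift of 0.1 to 0.3 SD and should not be read as an estimate. The conclusion also assumes that the statement on awareness of allocation includes the COTAPP examiner. The primary outcome, KIDSCREEN-27, is not touched. The change is worth making because most of it costs almost nothing.

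**What to change.** 1. **Set the order of the parameters.** In Secondary outcomes, item F, and in the secondary analysis section, state that the cognitive conclusion rests on the computer-recorded parameters (speed, variability, accuracy). Examiner-coded help and activity are supportive, and the amount of help is reported by arm so that unequal help can be seen. Cost: a few sentences. This step alone does not deal with the indirect route, which is why help by arm and the next two steps are needed.
2. **Record awareness.** At each remaining T1 session, the examiner notes whether the child's allocation was known. Cost: one checkbox.
3. **Mask where existing staff allow.** Have remaining T1 COTAPP sessions given by someone who does not treat the child and has not been shown the allocation, and add this exception to the Randomization section. Cost: rota planning and restricted access to the allocation. The documents give no staffing figures, so this should not be made to depend on an added assessor.

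There are two drawbacks. Some families will disclose their arm. Because the trial is ongoing, masked and unmasked sessions may be mixed. The awareness record allows both to be examined. If all T1 sessions are already complete, the first step remains possible, together with a plain statement that COTAPP testing was not masked.
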